### Data collection and management

The data will be managed using the REDCap electronic data capturing platform (https://www.project-redcap.org/). Assessments will be conducted by research staff at each site who are blind to group allocation; participants will be invited to complete assessments virtually but can choose to complete them in person if offered by the recruiting research site. Research staff at each site will administer physical assessments virtually at the Vancouver site, in-person at the Montreal site, and both in-person and virtual at the Hamilton and Toronto site. Participants will receive a link to the questionnaires via REDCap and complete them independently before the scheduled physical assessments, with the option to respond by mail or over the phone. Participants will complete physical assessments and questionnaires at baseline, 9 weeks, and 18 weeks after enrollment (Table 6 and Supplementary Fig. 2, Additional File 1). Each assessment will take approximately 45 min to complete. The exercise professionals will not be blind to group allocation, and may collect data on participant attendance, or adverse events (e.g. falls) reported to them during exercise sessions. Participants are free to withdraw anytime from the intervention, assessment, or both.

**Table 6 Tab6:** Study events and timeline

Activity		Staff member	Pre-randomization		W 1–8	W 9	W 10–17	W 18
All participants	Review eligibility criteria	Staff	X					
	Obtain consent to release medical records	Staff	X					
	Verify vertebral fracture using X-ray reports	Staff	X					
	Informed consent	Staff	X					
	Technology consultation	Staff		X				
	Demographic and medical history information	Staff blinded		X				
	Questionnaires	Staff blinded		X		X		X
	Physical assessments	Staff blinded		X		X		X
	Exit interview	Staff unblinded						X
	Adverse events, falls, fractures	Staff blinded			X			
Immediate VIVA delivery	Intervention session	EP			X			
	Practice continued behaviour change						X	
Delayed VIVA delivery	Intervention session	EP					X	
Other	Fidelity	Staff unblinded			X			
	Exit interview with exercise providers	Staff blinded						X

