## Methods

### Trial design

The trial is a four-centre, pragmatic [24] (Supplementary Table 1, Supplementary Fig. 1, Additional File 1) [25], pilot hybrid type 1 effectiveness-implementation trial with two parallel groups, randomized in a 1:1 ratio and stratified by centre in variable-sized blocks (ClinicalTrials.gov Identifier: NCT06650410). Participants will be randomized to the following: (1) immediate receipt of VIVA intervention or (2) wait-list usual care control and delayed receipt of VIVA 10-week post-randomization. The randomization sequence will be created and uploaded to REDCap by the trial statistician. Randomization will take place after the baseline assessment; the exercise professional delivering the intervention (not blind to allocation) will access the randomization function in REDCap to determine the participant’s allocation and communicate it to them. Outcome assessors will be blind to group allocation. Participants will not be blind to group allocation because they will know what group they are assigned to.

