#### Implementation

We will assess participant and provider experiences via interviews conducted using a semi-structured interview guide and adherence to the prescribed exercise via the Wibbi app (participant preference). All participants will be invited to participate in the interviews, conducted virtually using Zoom (https://www.zoom.com). The goal of the interviews is to gather feedback on the study assessments and rehabilitation sessions, including participants’ preference for method of delivery. With consent, we will record two sessions per site, selected at random, and complete a fidelity checklist [18]. We will assess the length of time to obtain radiology reports and number of ambiguous radiology reports.

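### Table 6 gives the exit interview with the unblinded exercise professionals to blinded staff, which could reveal allocations if it precedes a site's last assessment

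*Protocol article*

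**What the plan says.** The Trial design section of the protocol article sets the rule: "Outcome assessors will be blind to group allocation". Data collection and management repeats it: "Assessments will be conducted by research staff at each site who are blind to group allocation". The same section says of the people who deliver VIVA that "The exercise professionals will not be blind to group allocation". Trial design explains how they come to know the arm: "the exercise professional delivering the intervention (not blind to allocation) will access the randomization function in REDCap", after which they tell the participant the result.

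Table 6 gives a staff label to most study activities. Questionnaires and physical assessments carry "Staff blinded". The participant exit interview and the fidelity check carry "Staff unblinded". The row "Exit interview with exercise providers", listed in the group headed Other and marked at week 18, carries "Staff blinded".

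On content, the Implementation section says: "We will assess participant and provider experiences via interviews conducted using a semi-structured interview guide". It gives the aim as feedback on the assessments and the rehabilitation sessions. It does not say who interviews the providers, or when in calendar time.

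**The concern.** The table keeps blinded staff away from the two other activities that would expose them to intervention delivery, namely the participant exit interview and the fidelity check. It then sends blinded staff to interview the people who looked up the allocations. A provider describing how sessions went could easily let slip who has started VIVA and who is still waiting.

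Week 18 is counted from each participant's enrolment, and a site may recruit for up to 5 months. One participant's week 18 can therefore fall while others at the same site still await assessment. If the interviewer also assesses those participants, the staff-administered chair stand and balance tests would no longer be blind for them. Week 9 matters most, because it is the only follow-up at which one arm has had VIVA and the other has not. The chair stand is also the measure on which the future trial is sized.

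**Working it through.** The plan gives no figure on this point to reproduce. The check has two parts.

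**1. Table 6 labels set side by side**

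| Activity | Staff label | Contact with allocation |
|---|---|---|
| Questionnaires, physical assessments | blinded | must be none, by the Trial design rule |
| Participant exit interview | unblinded | participant knows own arm |
| Fidelity check | unblinded | observes sessions |
| Provider exit interview | blinded | provider knows the arms of those treated |

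The last row is the odd one out. The reason for using unblinded staff in the second and third rows applies to it at least as strongly.

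**2. How many assessments could be pending**

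Inputs from the protocol article:
- 8 participants per site over up to 5 months (Recruitment and sample size).
- Assessments at 9 and 18 weeks after enrolment (Data collection and management).
- Randomization after the baseline assessment (Trial design).

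Assumptions, not in the document:
- Entry is evenly spaced, and randomization coincides with entry.
- One provider knows all allocations made so far at the site.
- The interview takes place when the site's first participant reaches week 18.

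Spacing: 5 months is about 21.7 weeks, and 21.7 / 8 = 2.7 weeks. Entry falls at weeks 0, 2.7, 5.4, 8.1, 10.8, 13.5, 16.2 and 18.9.

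At calendar week 18:
- Already randomized means entry at or before week 18, which gives 7 participants. The eighth, entering at 18.9, has no allocation to reveal.
- Week-9 assessment pending means entry after 18 − 9 = 9. Among those randomized, the entries are 10.8, 13.5 and 16.2, so **3** are pending.
- Week-18 assessment pending means entry after 18 − 18 = 0. Among those randomized, the entries run from 2.7 to 16.2, so **6** are pending.

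Sensitivity to the assumed entry pattern, at the same moment:

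| Pattern | Spacing (weeks) | Randomized by week 18 | Week-9 pending | Week-18 pending |
|---|---|---|---|---|
| 5 months, divided by 8 | 21.7 / 8 = 2.7 | 7 | 3 | 6 |
| 5 months, first to last entry | 21.7 / 7 = 3.1 | 6 | 3 | 5 |
| 4 months, first to last entry | 17.4 / 7 = 2.5 | 8 | 4 | 7 |

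The 4-month row reflects the planned rate of two per site per month, without the extra month allowed. The moment chosen also matters a little. On the 2.7-week pattern, an interview between week 18.9 (eighth entry) and week 19.8 (10.8 + 9) would find 4 and 7 pending. After the site's last week-18 assessment, at 18.9 + 18 = 36.9 weeks, both counts are 0.

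**The case against.** The strongest reply is that an exit interview with a provider naturally comes when that provider has finished delivering, not when the first of up to eight participants reaches week 18. The row stands under Other, not under all participants or an arm, which fits that reading. The article is condensed, and Table 8 mentions a data collection manual that may settle the timing. This stands in part: the article's silence on calendar timing is not itself a fault. The staff label, however, is stated and conflicts with the blinding rule.

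The article also does not say that the interviewer assesses that provider's participants, and the stated aim of the interviews does not call for case-by-case discussion of allocation. This stands too: disclosure is a possibility, not a planned event. By week 18 both arms are scheduled to have received VIVA, so talk of delivering sessions does not by itself identify an arm at that visit. The week-18 counts therefore weigh less than the week-9 counts.

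Two stronger readings are tempting. A reader might infer that assessor blinding in this trial is broken. The document does not support that, because neither the interviewer's identity nor the calendar timing is fixed. A reader might also count everyone at the site and report 4 of 8 week-9 and 7 of 8 week-18 assessments at risk at week 18. On the 2.7-week schedule, that includes a participant who is not yet randomized.

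**Conclusion.** The inconsistency is real and minor, and it looks more like a labelling slip than a chosen design. If provider interviews start as early as the first participant's week 18, about 3 week-9 and 6 week-18 assessments of randomized participants per site could be exposed. Across the assumed entry patterns the range at that moment is 3 to 4 and 5 to 7. Exposure is nil if the interviews follow the site's last assessment, or if the interviewer does not assess that site's participants.

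The consequence is confined to the assessor-rated chair stand and balance tests; questionnaires are mostly self-completed. The Analyses section makes between-group comparisons exploratory and rules out clinical inference from them. Recruitment, retention and session attendance do not depend on assessor blinding, so the feasibility criteria are unaffected.

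**What to change.** In Table 6, change the staff label for the provider exit interview to "Staff unblinded", so that the staff who already conduct the participant exit interviews also interview the exercise professionals. Alternatively, keep the label and state that provider interviews take place only after the site's last week-18 assessment. The cost is one table cell or one sentence, with no extra staff and no change to sample size, schedule or analysis. Making the change now also keeps the inconsistency out of the procedures carried into the larger trial.

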### Primary outcome: feasibility

The feasibility outcomes are recruitment, adherence to the rehabilitation sessions, and retention. A future trial will be feasible if as follows: (a) we recruit eight people per site in 5 months, (b) adherence to the virtual rehabilitation sessions is 75%, (c) 80% of participants complete the trial. We will report recruitment as the number of participants recruited by each site, adherence as the proportion of scheduled virtual rehabilitation sessions participants attend, and retention as the proportion of participants who complete the final assessment out of the total number of participants. The exercise professional will record attendance to sessions.

### Secondary outcomes

#### Reach

We will collect data on PROGRESS-Plus factors (Place; Race/ethnicity/culture/language; Occupation; Gender and sex; Religion, Education; Socioeconomic status; Social capital) to describe participants [32]. To understand the participant population recruited and participant preferences, we will report the numbers of individuals recruited who are ≤ 12-week versus > 12-week post-vertebral fracture and those who attend outcome assessments in-person versus virtually.


#### Adoption

We will assess the number of screened and enrolled patients by referral source.

#### Implementation

We will assess participant and provider experiences via interviews conducted using a semi-structured interview guide and adherence to the prescribed exercise via the Wibbi app (participant preference). All participants will be invited to participate in the interviews, conducted virtually using Zoom (https://www.zoom.com). The goal of the interviews is to gather feedback on the study assessments and rehabilitation sessions, including participants’ preference for method of delivery. With consent, we will record two sessions per site, selected at random, and complete a fidelity checklist [18]. We will assess the length of time to obtain radiology reports and number of ambiguous radiology reports.

#### Maintenance (short term)

We will use adherence to the exercise sessions at the end of 18-week follow-up among the immediate group as a measure of short-term adherence.

#### Resource use

We will describe costs from a public payer perspective using data collected from participants throughout the study. At baseline and week 9, participants will complete a questionnaire to report the use of direct and indirect medical resources in the past 4 weeks and iMTA Productivity Cost Questionnaire for indirect resources. Multiplying resources collected by jurisdictional unit costs in Canadian dollars will determine the total cost. At baseline, week 9, and week 18, participants will complete EQ-5D-3L, which will be used as a measure of morbidity and potentially convert to (QALY).

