**Methods:**

The purpose of the study is to investigate the feasibility of a multicentre randomized controlled trial of an 8-week virtual rehabilitation intervention for people with an osteoporotic vertebral fracture in Ontario, British Columbia, and Quebec. The design is a multicentre randomized controlled trial with two parallel groups randomized in a 1:1 ratio, stratified by centre to immediate or delayed (10 weeks after randomization) receipt of the Virtual Intervention for Vertebral frActures (VIVA). Four centres will each recruit eight individuals (total *n* = 32) over the age of 50 who have had at least one vertebral fracture in the past 2 years confirmed by a radiology report. VIVA involves once weekly virtual rehabilitation sessions delivered over 8 weeks by an exercise professional, covering four areas: pain management, safe movement, exercise, and nutrition. Exercise professional provides resources and prescribes exercise therapy for participants to implement outside of the scheduled sessions. The primary feasibility outcomes are recruitment, retention, and adherence, and criteria for success are as follows: (a) recruiting eight people per site in 5 months, (b) 80% of participants completing the trial, and (c) 75% adherence to the virtual rehabilitation sessions. The secondary outcomes include costs relative to benefit, effects on health-related outcomes (e.g. 30-s chair stand, Brief Pain Inventory, Quality of Life Questionnaire of the European Foundation for Osteoporosis-41, SCREEN-14), and outcomes related to implementation (e.g. participant and provider experience using semi-structured interviews, fidelity, number of screened and enrolled participants by referral source, fracture verification process). Descriptive analyses (e.g. mean, count, percentage) will be performed for primary feasibility outcomes and secondary outcomes.

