### Intervention

#### Setting and supervision

The virtual one-on-one rehabilitation sessions will take place over the Zoom platform between the participant and the exercise professional (i.e. physical therapists, clinical exercise physiologists, or kinesiologists who have experience treating people with osteoporosis). The intervention includes eight-weekly sessions, each 45 to 60 min in duration. Participants will receive a technology consultation 1 to 2 weeks prior to the baseline assessment [28].

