##### Structure and description of the VIVA intervention

The exercise professionals will receive two 1-h training sessions and an intervention manual. During the training, the exercise professionals will learn about the structure of each session, the comprehensive content of each topic, and guidance on exercise prescription. Before virtually meeting the participant, the exercise professional will send education resources to the participant and review answers from the demographic and medical history, nutrition risk, quality of life, and falls self-efficacy questionnaires to inform intervention tailoring. Each session includes three components: (1) Education on a chosen topic supported by education materials, (2) training on or modeling of exercises, movement strategies, or pain management tips (including learning new ones or building on/progressing existing ones); and (3) delivery of behaviour change techniques to elicit maintenance of health behaviour, such as goal setting, action planning, and problem-solving to address barriers to change. At the end of each session, the participant and exercise professional will discuss the area of focus for the next session (e.g. pain management, safe movement, exercise, nutrition) and schedule the next session. The exercise professional will deliver the prescribed exercises and any educational resources (print and video) through the Wibbi app based on discussion with the participant. Participants will use the Wibbi app for self-monitoring of adherence to prescribed exercises; they can choose to receive all materials by mail and report adherence to prescribed exercise during the rehabilitation sessions directly to the exercise professional. Nutrition education includes common concerns such as unintended weight loss, loss of appetite, constipation, and strategies to manage them (e.g. examples of nutrient- and calorie-dense foods, the recommended daily intake of protein, calcium, and vitamin D). The education is supported by one-page summaries and a video series on dietary protein intake [31]. Pain management education and training will cover pain expectations and self-management tips such as avoiding prolonged sitting, slowly building activity tolerance, and applying cold or heat and cues on movement and positioning. Safe movement education and training addresses how to modify movement to reduce pain or fracture risk (e.g. example activities that may need to be modified and how to modify). There is some overlap between the categories of safe movement and pain education because movement education can be used to manage pain, but safe movement is included separately because it is not only related to pain. Individuals with spine fractures often experience fear of future fractures and want to know how to move safely and return to their activities of daily life. The examples include training sitting erect rather than with a flexed spine, hip hinge for bending, and getting up and down from the floor; education on strategies to reduce loads on the spine, hip hinge, and getting up and down from the floor; and education on strategies to reduce loads on the spine.

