### Analyses

All analyses (Table 7) will be performed using SAS version 9.2 (Cary, NC, USA). The reporting is guided by CONSORT, SPIRIT, SAGER, and SIITHIA guidelines [37–39]. See Table 8 for Template for Intervention Description and Replication (TIDieR) checklist and Additional File 2 for SPIRIT checklist. Participant characteristics will be reported using mean (standard deviation (SD)), median (interquartile range (IQR)), or count (percentage). For the primary outcomes, we will report recruitment, adherence, and retention using count and percentage (95% confidence interval [CI]). We will use descriptive statistics and narrative or graphical means to report reach, effectiveness, adoption, maintenance, and resource use outcomes for quantitative data using an intention-to-treat approach and use content or reflexive thematic analysis for qualitative data [40]. We will report the between-group difference in effectiveness and maintenance outcomes as mean (SD) or median (IQR), percent change, and 95% CI. Analyses of between-group differences will be exploratory, and no clinical inferences will be made. There will be no interim analyses or stopping rules.

**Table 7 Tab7:** Variables, hypotheses, outcomes, and methods of analysis

Variable	Criteria for feasibility/hypothesis	Outcome measure	Methods of analysis
Primary feasibility outcomes			
Recruitment	We will recruit 32 participants, 8 per site, in 5 months	Number of participants recruited at each site	Descriptive statistics
Adherence	Adherence to the rehabilitation sessions will be 75%	The proportion of scheduled sessions participant attended	
Retention	80% of our sample will complete the trial	The proportion of participants who complete the final assessment out of the total number of participants	
Secondary clinical/implementation outcomes			
Reach	N/A	• Number of participants categorized by PROGRESS-Plus factors • Number of individuals recruited who are ≤ 12-week versus > 12-week post-vertebral fracture • Number of people who attend outcome assessments in-person versus virtually	Descriptive statistics and narrative or graphical means

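### The total-cost rule has no provider-side input, so the immediate arm's described cost at week 9 omits about half or more of VIVA delivery at full attendance

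*Protocol article*

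**What the plan says.** The Resource use section of the protocol article sets the perspective and the data source together: "We will describe costs from a public payer perspective using data collected from participants throughout the study". It names two instruments, both completed by participants at baseline and week 9. In the first, "participants will complete a questionnaire to report the use of direct and indirect medical resources in the past 4 weeks". The second is the iMTA Productivity Cost Questionnaire. The costing rule follows: "Multiplying resources collected by jurisdictional unit costs in Canadian dollars will determine the total cost". EQ-5D-3L is collected at baseline, week 9 and week 18, with possible conversion to QALYs.

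The abstract describes the purpose this way: "The secondary outcomes include costs relative to benefit". Table 7 lists resource use as exploratory, with cost as the measure and descriptive statistics as the method.

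The inputs that VIVA itself consumes are described elsewhere. Under Setting and supervision: "The intervention includes eight-weekly sessions, each 45 to 60 min in duration". Under Structure and description of the VIVA intervention: "The exercise professionals will receive two 1-h training sessions and an intervention manual". That section also has the exercise professional send resources and review the participant's questionnaires before the first meeting, and use the Wibbi app to deliver exercises and education. Under Primary outcome: "The exercise professional will record attendance to sessions". The article uses that record for adherence and does not link it to cost.

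**The concern.** VIVA is supplied by the trial. The quantities that drive its cost (professional time, training, preparation, app access, print and mail) sit with the sites, not with participants. A total defined as participant-reported resources times unit costs describes the other care people used. At best it picks up part of VIVA.

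The stated perspective is that of a public payer, who would have to fund the sessions if VIVA were adopted. The benefit side (EQ-5D, possibly QALYs) reflects all of VIVA, while the cost side would reflect only a fraction. The error has one direction and, at the only post-baseline cost collection, falls on one arm. A pilot is also where the costing method for the larger trial should be tried out, so a gap here is likely to be carried forward.

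**Working it through.** The article states no cost figure, so there is nothing to reproduce. The check has three parts.

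**1. Does any section add provider-side cost?** The sections on the intervention, data collection, primary outcome, resource use and analyses, together with Tables 6 to 8, were read for this. None puts a cost on exercise-professional time, training, preparation, the app or materials. The only rule for total cost is the one in Resource use.

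**2. How much provider time is outside the rule?** Inputs: 8 sessions of 45 to 60 minutes, one-on-one (Setting and supervision); 32 participants randomized 1:1, so about 16 per arm; 75% attendance as the article's own adherence criterion.

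- Per participant, full attendance: 8 × 45 min = 360 min = 6 h; 8 × 60 min = 480 min = 8 h.
- Per participant at 75%: 0.75 × 6 = 4.5 h; 0.75 × 8 = 6 h.
- Immediate arm of 16, full attendance: 16 × 6 = 96 h; 16 × 8 = 128 h.

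Training (two 1-hour sessions per exercise professional), preparation, app and materials come on top. The article does not give the number of professionals or these unit costs.

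**3. How much could the questionnaire recover?** The items are not shown, so both cases are taken. Immediate-arm sessions run in weeks 1 to 8 and the questionnaire is at week 9.

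- VIVA sessions not listed by participants: 0 of 8 recovered.
- Listed, with the 4-week window covering weeks 5 to 8: 4 of 8 recovered, i.e. 3 to 4 h. The other 3 to 4 h are missed.
- Listed, with the window covering weeks 6 to 9: 3 of 8 recovered, i.e. 2.25 to 3 h. The other 3.75 to 5 h are missed.

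At full attendance, therefore, between half and all of the contact time is left out. In every case training, preparation and licence costs are also left out, because participants have no means of reporting them. With 6 of 8 sessions attended, at most 4 can fall in the window, so at least 2 sessions (1.5 to 2 h) are still missed.

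**Money, as an assumption only.** At CAD 40 to 150 per hour, 6 h × 40 = CAD 240 and 8 h × 150 = CAD 1,200 per participant at full attendance, before any self-reported sessions are deducted. The article supports no particular rate.

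**The case against.** The strongest reply is that a short section of a journal article is being read too narrowly. It never says that delivery cost is excluded, attendance is recorded during the study, and detailed intervention costing is often left to a full protocol or economic analysis plan. That would answer a complaint about missing detail. It does not answer this point, because the article states a positive rule: participants are the source, two participant instruments are named, and the product determines the total. Counting attendance logs kept by the exercise professional as resources reported by participants stretches that wording.

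Other parts of the reply stand.

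- The questionnaire items are not shown, so a reader may not conclude that it captures nothing of VIVA. Some sessions may be listed.
- A reader might infer that the trial will report a biased between-arm cost comparison, or declare VIVA cost-saving. The documents do not plan that. The Analyses section says: "We will use descriptive statistics and narrative or graphical means to report reach, effectiveness, adoption, maintenance, and resource use outcomes". It confines reported between-group differences to effectiveness and maintenance outcomes and treats them as exploratory. QALY conversion is only a possibility, and no cost-effectiveness ratio is specified.
- A reader might multiply the hours by all 32 participants. The delayed arm receives VIVA in weeks 10 to 17, after the last resource questionnaire, so the week-9 understatement concerns about 16 people.
- That delivery is the main cost VIVA adds is plausible given 6 to 8 hours of professional time, but no figure in the article establishes it.
- Much can be recovered later, since attendance is recorded and session length and training hours are set out. This limits the harm but does not correct the stated rule.

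**Conclusion.** The point holds in this form: followed as written, the rule gives a week-9 total cost for the immediate arm that is too low by 6 to 8 h of scheduled provider time per participant (4.5 to 6 h at 75% attendance; 96 to 128 h for an arm of about 16 at full attendance), less whatever sessions participants report themselves, and with training, preparation, app and materials also absent. It rests on three things: the article's description of its instruments, no provider-side costing elsewhere in the article, and session lengths as planned. The dollar value is unknown.

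Recruitment, retention and adherence are unaffected. The consequence is confined to an exploratory cost description that, set against benefit, would favour VIVA and give a poor basis for planning the larger trial's economic evaluation. It should be corrected, but it does not threaten the study's main purpose.

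**What to change.** In Resource use, define total cost as the sum of two parts and report them separately:

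- participant-reported resources that fall to the public payer, times unit costs;
- VIVA delivery cost: sessions delivered (from the attendance records) × session duration × wage rate, plus training, preparation, app licence and materials, excluding costs incurred only for research.

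Add one instruction to the resource questionnaire asking participants not to list VIVA sessions, so that they are neither partly missed nor counted twice.

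The cost is small. Attendance is already recorded, and session length and training hours are set out. What is new is a wage rate, a short log of preparation time, licence and materials invoices, and some analysis work. The immediate arm's stated cost will look less favourable.
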